## General Information

### Title

Promoting activity for frail aged in post-acute care hospital settings: a randomized controlled trial of accelerometry

**Short Title:** Promoting activity in geriatric rehabilitation

### Funding

National Health and Medical Research Council Project Grant 2011-2013

### Project ID

**NHMRC ID** APP: 1007886

**Australian New Zealand Clinical Trials Registry** registration number ACTRN12611000034932

## Background Information

### Rationale

For frail older people, low levels of mobility during hospitalization are associated with functional decline and deconditioning (decline in muscle strength and bulk as a result of physical inactivity), leading to increased length of stay, post discharge readmission or transfer to permanent residential care [1]. While the importance of physical activity in the functional recovery of older rehabilitation patients has been recognised, questions remain about the optimal methods to promote and monitor activity for frail older people in post-acute hospital settings [2].

Observational studies [3,4] have shown that activity levels in older people undergoing in-patient rehabilitation are low. Essential activity (such as toilet visits) accounted for 3.4% of waking hours, whilst self-directed physical activity accounted for only 0.4% of the patient's time. Patients spent 65% of daytime hours either asleep or completely inactive [3]. The factors that contribute to low activity in rehabilitation have not been well studied. One survey of older patients in a post-acute hospital setting found that whilst attitudes to exercise were generally positive, patients over-estimated the adequacy of their activity levels. They were unsure if they should be doing more exercise and frequently stated health problems as a barrier to increased activity. Only 11% recalled having been advised to exercise regularly by a health professional [5].

Rehabilitation for older people should have specific goals, set in conjunction with the patient, family members and multi-disciplinary team [6]. Goal-setting enhances both the process and outcome of clinical care and is a core practice in rehabilitation [7]. To restore physical function and independence in frail and deconditioned patients, it is important to set measurable, attainable mobility goals and to monitor progress carefully [2]. Monitoring and feedback are essential tenets in health promotion strategies to change behaviour, since exercise is significantly influenced by self-efficacy (confidence in one's ability to exercise) and exercise outcome expectations [8]. The setting of activity targets (such as achieving a particular heart rate or step count) has been used to increase levels of physical activity in healthy older people [2]. However, measuring and targeting activity in older patients in rehabilitation settings using models of exercise prescription and monitoring developed for healthy individuals may not be appropriate or accurate [2].

Current methods for prescribing activity for older hospitalised patients are to ask staff to walk patients on a regular basis and monitor what they do. Such walking programs have been successfully implemented in acute care settings, with reported outcomes such as increases in mobility and independence [8]. However such ad hoc programs are expensive, resource intensive and are unlikely to produce a measurable output. Alternatively, we have the opportunity to utilise accelerometry for continuous, unsupervised, objective monitoring of mobility.

Pedometers, widely used to promote physical activity [9] are inaccurate when assessing step counts as a measure of activity in elderly populations with varying levels of physical dysfunction and gait anomalies [10]. Advances in technology over the past decade have led to the development of wearable devices, such

as accelerometers, with potential for continuous ambulatory activity monitoring of older adults in clinical settings [1]. Such devices have been used in research studies of gait and balance analysis for falls risk assessment and to detect posture changes for activity monitoring in groups such as amputees, medical and surgical patients, and those with Parkinson's disease, diabetes, stroke and multiple sclerosis [1].

The study proposed in this protocol is one of a series designed to explore the efficacy of accelerometry in rehabilitation and geriatric assessment services in hospital.

## Research Plan

The study proposed here is one of a series designed to explore the efficacy of accelerometry in rehabilitation and geriatric assessment services in hospital.

### Aims

The primary aim of this proposal is to test whether activity levels can be increased by the provision of accurate activity data to patients and clinicians in the context of explicit goal setting. Secondary aims are to explore the effects of increased walking activity (if achieved) on patient outcomes and undertake a cost benefit analysis.

### Hypothesis

The central hypothesis is that, in post-acute restorative care settings, the provision of activity data obtained by accelerometry, provided to patients and clinicians in the context of explicit goal-setting, will result in a mean increase of 33% in daily walking activity in the intervention group compared with controls offered standard care.

### Study design and setting

A parallel group randomised controlled trial will be conducted. The setting will be post-acute care Geriatric Rehabilitation Units or Geriatric Evaluation and Management Units at 3 sites (QLD, NSW, and SA) which have at least a 40 bed capacity.

### Subjects

Patients admitted to post acute care rehabilitation who are (1) aged  $\geq 60$  years; (2) able to ambulate independently or with supervision, or who have a rehabilitation goal to become ambulant within the context of the current admission; and (3) expected to have a length of stay of at least 2 weeks, will be eligible to participate. Exclusion criteria will be those (1) with lower limb amputation; (2) with delirium/agitated dementia.

### Outcomes

The primary outcome measure will be walking time per day collected using the accelerometer. The accelerometer devices used in this study are tri-axial ALIVE Heart and Activity Monitors, manufactured by Alive Technologies Pty. Ltd. The device is 90mm X 40mm X 16mm, weighs 55g with the battery, and measures acceleration in 3 directions using a spring mass system. A single device is fitted in a pouch attached to a belt worn around the waist.

Secondary outcome measures will include lower extremity function and functional status, quality of life (QoL), length of stay, post discharge hospital readmissions or differences in level of care.

### Sample size and power analysis

The background information for sample size calculation is based on accelerometry pilot data of 60 patients with a mean (SD) daily walking time of 45 (51) minutes, correlation coefficient of 0.20 between baseline and 14 follow-up measurements and a correlation coefficient of 0.60 between the follow-up measurements. The power analyses are based on 14 and 20 days of possible repeated measures of daily activities. To observe an increase of activity by at least 15 minutes (33%) in the intervention group, 108 patients are required in each group with 14 days of measurements and 105 patients in each group with 20 days of measurements, with 80% power at 5% level of significance.

We will recruit 270 patients over a period of 12 months, allowing for an attrition rate of 20%. Based on a previous study that mobility activity level is strongly correlated (0.79) with functional independence as measured by the Barthel Index, we hypothesise that an increase in average daily walking time by 15 minutes (33%) would result in clinically significant gains in functional capacity.

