### Recruitment and randomisation procedure

The site coordinator will explain the study protocol with clinical staff and publicise the study within the rehabilitation wards.

The Research Assessor (RA) will liaise daily with the clinical coordinator and clinical staff to identify potential participants for the study then screen for eligibility. Patients who meet the eligibility criteria will be in either “eligible now” (ready to ambulate with or without supervision) or “potentially eligible in the future” (not ready to mobilise but who have a rehabilitation goal to become ambulant in the context of the current admission”. For those “eligible now” and if the device is available the RA will seek informed consent to participate. For those “potentially eligible in the future” the RA will continue to liaise with clinical staff to determine when the patient is ready to mobilise. As soon as ready to mobilize and the device is available, the RA will seek informed consent to participate using the Ethics approved Patient Information and Consent Forms.

As soon as a patient consents to participate, the RA will allocate a participant ID number- the first two digits will signify the site (01: QLD; 02: NSW; 03: SA) and the following 3 digits are the patient unique ID starting at 001 and consecutively until the recruitment target of 90 patients is reached (ie 090). The RA then gives the participant ID number to the Accelerometry Monitor (AM) who will open the envelope identified by ID

number and allocate to intervention or control group according to the code inside. Randomisation codes will be generated by the Queensland Clinical Trials and Biostatistics Centre. The RA is blinded as to group allocation.

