### Study procedure

For both groups the AM will show the study participants how to put on the accelerometer belt which they are required to wear from rising to going to bed (and for at least 8 hours) each day over the study period. The participant will remove the accelerometer belt in the evening and when showering. The AM will monitor and record the level of compliance with wearing the accelerometer. In addition the AM will obtain from the treating physiotherapist the daily time spent in therapy sessions.

For each participant, the duration of the study is expected to be 28 days (4 weeks) unless in the interim, the patient is discharged or unable to continue in the study by virtue of a sudden change in condition which precludes mobility. Each weekday morning, the AM will download data from the accelerometers for daily readings of walking time, (and other activity measures).

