### Intervention group

At commencement, the treating physiotherapist will be asked to discuss with the intervention participants their mobility goals, including provisional targets for daily walking time. These goals will be re-examined and modified, informed by the accelerometer data, to motivate the patient to improve activity levels and reach set targets. **The walking time targets are based on walking time outside of therapy sessions.** Information provided to the treating physiotherapists and the participants will include daily walking time outside therapy as well as daily walking time targets in numerical and graphical form. The targets will be reviewed daily until discharge or 4 weeks, whichever comes first. Walking times over a week will be summarised in chart form and made available at the weekly case conference. Staff will be trained in the use of accelerometry data and be asked to encourage patients to meet their activity goals.

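### The sample size takes credit for a baseline walking-time value that the procedures do not collect; without it, power for complete patients is about 78% (14 days) or 77% (20 days), not 80%

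*Protocol*

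**What the plan says.** The Outcomes section defines the endpoint: "The primary outcome measure will be walking time per day collected using the accelerometer".

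The section on sample size and power draws on "accelerometry pilot data of 60 patients with a mean (SD) daily walking time of 45 (51) minutes". Its next input is a "correlation coefficient of 0.20 between baseline and 14 follow-up measurements", and it pairs this with "a correlation coefficient of 0.60 between the follow-up measurements". It continues: "The power analyses are based on 14 and 20 days of possible repeated measures of daily activities". For a 15-minute (33%) difference with 80% power at the 5% level it states 108 patients per group with 14 days and 105 with 20 days. It then recruits 270 to allow for 20% attrition.

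The procedures run in this order:

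- Recruitment and randomisation procedure: "As soon as a patient consents to participate, the RA will allocate a participant ID number". The ID goes to the Accelerometry Monitor, who opens the matching envelope.
- Study procedure, on first use of the device: "For both groups the AM will show the study participants how to put on the accelerometer belt".
- Intervention group, on target setting: "At commencement, the treating physiotherapist will be asked to discuss with the intervention participants their mobility goals, including provisional targets for daily walking time".

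Data Collection gives entry time points for the Short Physical Performance Battery, the interRAI instrument, the self-efficacy scales and EQ-5D. It gives none for walking time. Analysis compares repeated daily walking times between the groups and names no baseline walking value.

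**The concern.** A correlation between baseline and follow-up reduces the required sample size only if a baseline is measured and used. Here the calculation appears to rely on one, while the procedures go from consent to allocation with no day of wear in between.

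Two things are at stake. The stated 80% power rests on a measurement that is not described. And whoever writes the analysis to match the calculation may take the first day of wear as the baseline. That day falls after allocation, and in the intervention group it may already reflect a provisional target. Adjusting for it could remove part of the treatment effect.

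**Working it through.** **Inputs (Protocol, Sample size and power analysis).** SD 51 minutes; difference 15 minutes; baseline correlation 0.20; follow-up correlation 0.60; 14 or 20 follow-up days; 80% power; 5% level. Assumed here: two-sided test, constant SD, compound symmetry.

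**Formula.** n per group = 2 × (1.96 + 0.8416)² × 51² / 15² × F = 181.47 × F, where F is the variance of the analysed quantity relative to a single day.

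**Step 1: reproduce the stated figures with a baseline.** F = (1 + (r − 1) × 0.60)/r − 0.20².

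- r = 14: F = 8.8/14 − 0.04 = 0.5886; n = 106.8, rounded up 107 (stated 108).
- r = 20: F = 12.4/20 − 0.04 = 0.5800; n = 105.3, rounded up 106 (stated 105).

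With a noncentral t instead of the normal approximation, the results are 108 and 107.

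**Step 2: other designs with the same inputs.**

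| Design | 14 days | 20 days |
|---|---|---|
| Stated | 108 | 105 |
| Baseline-adjusted, two-sided | 107 | 106 |
| Mean of follow-up days only | 115 | 113 |
| Change from baseline | 223 | 222 |
| Baseline-adjusted, one-sided | 85 | 83 |

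Of these, only the two-sided baseline-adjusted design comes close to both stated figures.

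**Step 3: remove the baseline term.** F = (1 + (r − 1) × 0.60)/r.

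- r = 14: F = 0.6286; n = 114.1, so 115 per group. At 20% attrition: 230/0.8 = 287.5, so 288 recruited.
- r = 20: F = 0.6200; n = 112.5, so 113 per group. At 20% attrition: 226/0.8 = 282.5, so 283 recruited.

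The protocol recruits 216/0.8 = 270.

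**Step 4: power at the stated sizes.** Power = Φ(15 / (51 × √(2F/n)) − 1.96).

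| | With baseline | Without |
|---|---|---|
| 14 days, 108 per group | 80.4% | 77.8% |
| 20 days, 105 per group | 79.9% | 77.2% |
| 20 days, 108 per group | 81.0% | 78.4% |

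More wear days do not quite replace the baseline. As r grows without limit, F tends to 0.60 and n to 181.47 × 0.60 = 108.9, still just above 108.

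**Step 5: what early leavers could add (14 days, no baseline).** Recruiting 270 gives 135 per group, of whom 27 are counted as lost. A patient with one day carries 0.6286 of the information of a complete patient. If all 27 give one day, the total is 108 + 27 × 0.6286 = 125 complete-patient equivalents, and power is 83.5%. To reach 114.1 takes (114.1 − 108)/0.6286 = 9.7, so about 10 of the 27.

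**The case against.** **The gap is small and may not materialise.** It is 2 to 3 points. The analysis is by intention to treat on repeated daily measures, so patients who leave early can contribute days; Step 5 shows that about 10 of 27 leavers per group with one day each would close it at 14 days. At 15% attrition, 270 × 0.85 / 2 = 114.75, about 115 per group, would remain. The pilot SD is also far less certain than this: with 60 patients and normal theory, the 95% interval is 51 × √(59/82.12) = 43.2 to 51 × √(59/39.66) = 62.2, which moves the baseline-adjusted requirement from about 77 to about 159. All of this stands. A reader might infer that the trial cannot reach 80% power; the documents do not support that. What remains is that the protocol's own calculation counts complete patients and does not give 80% for them without a baseline.

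**The method is inferred.** The protocol names no formula, and the rounded figures miss by one in opposite directions. This too stands, but the 0.20 baseline correlation is stated as an input, and the designs without it miss by more.

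**Covariates belong in the statistical analysis plan.** So they do, and that plan is not shown. But it cannot create a measurement that the procedures do not take. The companion Study Guidelines, also not shown, might define a run-in day; the protocol's sequence from consent to envelope reads otherwise.

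**The bias from a day-1 covariate is hypothetical.** A reader might infer that the effect estimate will be badly diluted: if day 1 carried the full effect, adjustment would take the expected estimate from 15 to 15 − 0.20 × 15 = 12 minutes, and power to about 61%. The documents do not support that figure. Nothing in the protocol names day 1 as a covariate. Data are downloaded on weekday mornings, so no accelerometer feedback exists during the first day of wear, and only a provisional target could act. The protocol does not say whether the physiotherapist's discussion precedes that day. The direction of the risk is sound; its size is unknown.

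**Conclusion.** The point holds in a limited form. The stated 108 and 105 per group depend on a baseline walking-time value that the procedures do not collect before allocation. On the protocol's own inputs, without that baseline, power for complete patients is about 78% (14 days, 108 per group) or 77% (20 days, 105 per group), and 80% would need 115 or 113 per group. This assumes a two-sided 5% test, compound symmetry, a constant SD of 51, and no contribution from patients counted as attrition.

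The inconsistency is worth correcting because it is clear on the page and because it invites a post-allocation day to be used as the baseline. A reader might also infer that a run-in day is essential. It is not: at the only documented correlation, 0.20, a true baseline is worth 2.6 power points at 108 per group.

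**What to change.** 1. In Sample size and power analysis, delete the 0.20 baseline correlation and restate power as about 78% for 108 complete patients per group. If early leavers' partial data are expected to restore 80%, say so and show the calculation.
2. In Analysis, state that a wear day after allocation will not be used as a baseline covariate, because in the intervention group it may already reflect the provisional target.

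These two changes cost only wording.

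As an alternative, if the sponsor finds it feasible: record one feedback-free wear day after consent and before the envelope is opened, name it as the baseline covariate, and exclude it from the follow-up days. The 0.20 term could then stay. The cost is a change to the recruitment sequence, possible losses between consent and allocation, and a delay to allocation of one day, or longer over a weekend if the envelope waits for a download, since downloads take place on weekdays only.

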### Feasibility of recruiting required sample size

Based on a conservative recruitment rate of 2 patients per week at each site, it would take 48 weeks to complete data collection for 90 patients (270 for the 3 sites) based on an average length of stay of 4 weeks. A minimum of 8 accelerometers would be required per site.

### Recruitment and randomisation procedure

The site coordinator will explain the study protocol with clinical staff and publicise the study within the rehabilitation wards.

The Research Assessor (RA) will liaise daily with the clinical coordinator and clinical staff to identify potential participants for the study then screen for eligibility. Patients who meet the eligibility criteria will be in either “eligible now” (ready to ambulate with or without supervision) or “potentially eligible in the future” (not ready to mobilise but who have a rehabilitation goal to become ambulant in the context of the current admission”. For those “eligible now” and if the device is available the RA will seek informed consent to participate. For those “potentially eligible in the future” the RA will continue to liaise with clinical staff to determine when the patient is ready to mobilise. As soon as ready to mobilize and the device is available, the RA will seek informed consent to participate using the Ethics approved Patient Information and Consent Forms.

As soon as a patient consents to participate, the RA will allocate a participant ID number- the first two digits will signify the site (01: QLD; 02: NSW; 03: SA) and the following 3 digits are the patient unique ID starting at 001 and consecutively until the recruitment target of 90 patients is reached (ie 090). The RA then gives the participant ID number to the Accelerometry Monitor (AM) who will open the envelope identified by ID

number and allocate to intervention or control group according to the code inside. Randomisation codes will be generated by the Queensland Clinical Trials and Biostatistics Centre. The RA is blinded as to group allocation.

### Study procedure

For both groups the AM will show the study participants how to put on the accelerometer belt which they are required to wear from rising to going to bed (and for at least 8 hours) each day over the study period. The participant will remove the accelerometer belt in the evening and when showering. The AM will monitor and record the level of compliance with wearing the accelerometer. In addition the AM will obtain from the treating physiotherapist the daily time spent in therapy sessions.

For each participant, the duration of the study is expected to be 28 days (4 weeks) unless in the interim, the patient is discharged or unable to continue in the study by virtue of a sudden change in condition which precludes mobility. Each weekday morning, the AM will download data from the accelerometers for daily readings of walking time, (and other activity measures).

### Intervention group

At commencement, the treating physiotherapist will be asked to discuss with the intervention participants their mobility goals, including provisional targets for daily walking time. These goals will be re-examined and modified, informed by the accelerometer data, to motivate the patient to improve activity levels and reach set targets. **The walking time targets are based on walking time outside of therapy sessions.** Information provided to the treating physiotherapists and the participants will include daily walking time outside therapy as well as daily walking time targets in numerical and graphical form. The targets will be reviewed daily until discharge or 4 weeks, whichever comes first. Walking times over a week will be summarised in chart form and made available at the weekly case conference. Staff will be trained in the use of accelerometry data and be asked to encourage patients to meet their activity goals.

